**Fig. 1 Fig1:**
[figure not shown]
The Move for Life peer mentor model cascading professional impact

Move for Life aims to augment and complement existing physical activity programmes in counties Clare (with a population of 117,000) and Limerick (with a population of almost 200,000) in the Mid-West region of Ireland initially. The University of Limerick, where most of the academic team is based, has research links with the Local Sports Partnerships of counties Limerick and Clare. These counties cover one whole Health Service Executive Community Health Organisations (HSE CHO) area. These counties, both with distinctive urban dwelling and rural populations, were selected both for convenience to the academic location and for their potential to replicate the national demographic.

A well-designed, rigorously conducted randomised controlled cluster trial (RCT) is required to provide evidence of potential for a comprehensive MFL intervention. Prior to such a definitive trial, a feasibility study is required. MFL will provide this using a feasibility cluster RCT design; it will advise the selection of RCT primary and secondary outcomes and develop our understanding of the impact on hard to reach inactive adults from the professional-peer-participant cascading model of intervention. The purpose of MFL is to increase the daily time spent in MVPA among inactive people aged 45 and over.

The study hypothesis is that it is feasible to deliver the MFL intervention and to measure the time spent in daily MVPA by participants. Therefore, the primary aim is to investigate the feasibility of the trial and data collection. Specific objectives are to record numbers recruited, retention and attrition rates, safety and acceptability of the intervention and measurements and follow-up testing attendances and participant compliance. The secondary aim is to obtain preliminary information on the economic impact of the trial on participants. Accordingly, secondary objectives are to collect data on health costs and quality of life for participants in each arm of the study for the duration of the trial (Fig. 1).

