### Study overview

The trial is set in eight Local Sports Partnership (LSP) hubs that have ongoing structured physical activity programmes. LSPs are state-funded community-based organisations whose specific purpose is to provide approved and structured physical activity classes for the communities they serve, using professional instructors. Eligible participants will contact one of eight regional hubs, with each hub running four physical activity programmes. These include Men on the Move, Women on Wheels, Go for Life and Get Ireland Walking. Each hub will be randomised to one of the following: true control, usual programme or MFL intervention. The intervention will augment existing programmes by training professional instructors to implement individual and group-based behaviour change strategies, assisted by peer mentors that will help keep the group together after the lifetime of the programme. The true control group will be given information about physical activity but will not be included in a programme for the duration of the study; usual programme groups will have physical activity classes delivered as normal. Baseline data will be collected on physical activity measures and follow-up measurements will be obtained at 3 and 6 months. Participants in all groups will be asked to wear a lightweight device for measuring activity on the thigh (an activPAL) for 1 week before commencing the programme and again at 3 and 6 months. An Adverse Events Reporting System will be in place, reporting back to the Move for Life advisory committee, who will make decisions about trial safety and continuance. Ethical approval for the study was granted by the University of Limerick, Faculty of Education and Health Sciences Research Ethics Committee (reference number—EHS_2018_02_15, approved on April 9, 2018) (Fig. 2).

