### Randomisation process

The hubs will be the unit of randomisation and will be randomised to each arm. Each hub (cluster) will be geographically separated to reduce contamination effect. Clusters will be stratified as rural or urban. Hubs will be randomised to one of the following: true control (two hubs), usual programme (three hubs) or MFL intervention (three hubs). Participants in the true control group will be given information about physical activity but will be placed on a waiting list for access to the MFL physical activity programmes for the duration of the trial. They will be offered the programmes after the trial. The participants allocated to the MFL intervention group and the usual physical activity programmes will not be aware of their status. Randomisation will only occur and will only be revealed to participants and their instructors after all the baseline data have been collected.

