The MFL peer mentor will receive training from the MFL team, which will provide advice on how to maintain the group post 8/12 weeks formal programme. This training will provide information and organisational support and identify social and environmental supports for physical activity locally. Additionally, during the MFL programme, individuals who show an interest in helping to sustain the programme, post involvement of the professional, will be identified by the MFL instructor and the peer mentor, and these emerging assistants will be provided with support to contribute to the sustainability of the programme. At the end of the MFL programme, the assistants will receive training to become a new MFL peer mentor. An ‘augmented’ physical activity program has been conceptualised with a clearly defined behaviour change focus and related activities for each week. It can be adapted for 8, 10 or 12 weeks depending on the duration of the particular MFL programme strand. It will not be possible to blind the professional instructors as they will have to learn the techniques developed for the MFL intervention. Final details of the intervention are currently being completed by a multidisciplinary team.

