## Outcomes

The primary outcome of the study is to investigate the feasibility of measuring MVPA. The acceptability and safety of the intervention and measurement methods will be investigated. The data will provide reliable estimates for sample size calculation for a future definitive trial. Secondary outcomes relate to data on recruitment, allocation, retention, attrition and attendance. Data will be collected on safety and adverse events will be recorded by the LSP tutor. Participant recruitment outcomes include demographic profile and the success of each of the recruitment strategies. Participant retention outcomes include the number, profile and reasons of participants that drop out. Data will be collected on the numbers who complete each part of the physical activity measures and questionnaires and who wear and return the activPAL devices. Questionnaires will enable the collection of data on healthcare resource use, out-of-pocket expenses and health-related quality of life. For each secondary outcome, the point estimate of effect will be reported, and precision will be presented with 95% confidence intervals. SPSS version 25 will be used for the statistical analyses. At specific time-points, immediately post intervention and 3 months post intervention, follow-up testing sessions will take place. The authors define ‘minimum thresholds’ in the context of the post intervention and 3-month follow up testing as the minimum proportion of participants that attend the testing sessions and provide reliable data.

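### The only named adverse-event recorder is the class tutor, so no recorder is named for the true-control hubs, the post-class months or the measurement sessions

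*Protocol article*

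**What the plan says.** Safety is among the specific objectives under the primary aim in the Background, which lists "safety and acceptability of the intervention and measurements". The Outcomes section repeats the scope: "The acceptability and safety of the intervention and measurement methods will be investigated". It then assigns the recording: "Data will be collected on safety and adverse events will be recorded by the LSP tutor".

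The Study overview adds a trial-level route: "An Adverse Events Reporting System will be in place, reporting back to the Move for Life advisory committee", a body "who will make decisions about trial safety and continuance". It gives the destination of the reports but not who supplies them.

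On contact with tutors, the Study overview says that a true-control participant "will not be included in a programme for the duration of the study". The comparator section gives programme lengths of 12 weeks (two programmes) and 8 weeks (two programmes). In the MFL arm the peer mentor is trained in "how to maintain the group post 8/12 weeks formal programme". Follow-up is at 3 and 6 months in the Study overview, and immediately after and 3 months after the intervention in the Outcomes section.

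**The concern.** This is an explicit assignment of the task to a role that exists only where and while a class is running. Read together with the design, it leaves three parts of the trial without a named recorder:

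- the two true-control hubs;
- the months after the classes, which in the MFL arm include the peer-mentor-led continuation that distinguishes it from the usual programme;
- the measurements. Functional tests and the 7-day thigh-worn device are handled by the data collection team in every arm, and the first device wear precedes the programme.

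The third gap matters because the stated safety aim covers the measurement methods as well as the intervention. The advisory committee decides on safety and continuance, and the progression criteria contain no safety item, so the reporting route is the only safety check the article describes. If its input depends on class contact, a difference between a class arm and true control would partly or wholly reflect who was being watched.

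**Working it through.** **Size of the control arm.** The plan's own total comes first: 8 hubs × 4 programmes × 15 people = 480; 480 × 0.20 = 96; 480 + 96 = 576, as stated under Sample size justification. Allocation is 2 control, 3 usual programme and 3 MFL hubs (Randomisation process). With hubs of equal size (assumption), control is 2/8 = 25%, that is 120 of 480 or 144 of 576 participants with no named recorder.

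**Share of follow-up with a tutor.** Coverage in a class hub = class weeks ÷ follow-up weeks. The control hubs have 0 class weeks, so 0%.

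- Follow-up of 6 months taken as 26 weeks: 8/26 = 31% and 12/26 = 46%, leaving 18 and 14 weeks after the classes.
- Follow-up to programme end plus 13 weeks (the wording in Outcomes): 8/21 = 38% and 12/25 = 48%.
- Sensitivity, 6 months taken as 24 weeks: 8/24 = 33% and 12/24 = 50%.

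**Whole trial.** Coverage × 6/8, again with equal hubs:

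- 26 weeks: 0.75 × 8/26 = 23% to 0.75 × 12/26 = 35%.
- Programme end plus 13 weeks: 0.75 × 8/21 = 29% to 0.75 × 12/25 = 36%.
- 24 weeks: 25% to 38%.

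**Illustration only.** The article gives no adverse-event rate. Suppose the true rate r over 26 weeks is the same in every arm, the hazard is uniform, and tutors record every event in class weeks and none outside them. The recorded rate is then r × class weeks ÷ 26:

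| Assumed r | Class hubs, 8 to 12 weeks | Control hubs |
|---|---|---|
| 5% | 1.5% to 2.3% | 0% |
| 10% | 3.1% to 4.6% | 0% |
| 20% | 6.2% to 9.2% | 0% |

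The table shows the direction of the distortion under tutor-only capture. It is not a forecast.

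**MFL against usual programme.** Both arms run the same four programmes of the same length, so tutor coverage during classes is similar. After the classes neither has a named recorder, and only the MFL arm has a peer-mentor-led phase.

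**The case against.** The Outcomes sentence does not say that only the tutor records events. The reporting system in the Study overview is summarised in one sentence, and its procedures may be in the full protocol. The questionnaire and testing protocol are additional files not shown here, and either might already ask about events. This stands to the extent that the gap is one of no named recorder. A reader might infer that control participants have no recorder at all, but the article does not establish that. Even so, the one source it does name is tied to the classes, and nothing in the text extends it.

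A reader might also infer that the safety outcome is biased as a whole. The documents do not support that. No between-arm test of adverse events is specified, any hypothesis testing is exploratory, and a class-based recorder is a sensible source for the safety of classes as delivered. The distortion concerns class arms against true control. It would matter if events are tabulated by arm, or if the Outcomes section's promise of effect estimates with 95% confidence intervals for secondary outcomes is taken to include them.

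Nor does the article support saying that injured drop-outs go unseen, because the number, profile and reasons of those who drop out are collected. Questionnaire data on healthcare use are a further partial source, and the sports development officer supports peer mentors during the trial. Neither is given an adverse-event duty.

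**Conclusion.** The concern holds as a gap in stated ascertainment. Followed as written, the plan has tutor-covered time of 0% of follow-up in the two control hubs and about 31% to 48% in the six class hubs. It names no one to record events in the MFL peer-mentor-led phase or events caused by the measurements in any arm. A safety estimate of either class arm against true control would be confounded with ascertainment, while MFL against usual programme is comparably covered during classes only.

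The coverage figures rest on the programme lengths in the article, on reading follow-up as 26 weeks or as programme end plus 13 weeks, and on the tutor being the operative source. The whole-trial figures also assume hubs of equal size. The contrast of 0% with about 3% to 5% depends on an assumed 10% rate and tutor-only capture, and should not be cited as an expected result.

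**What to change.** - Add the same short adverse-event items (for example falls, injury, new symptoms and unplanned care since the last session) to the existing questionnaire at the 3- and 6-month sessions, for all participants in all three arms. Word them without reference to classes, since the testing team is to be blinded to each hub's allocation.
- Use this source for any between-arm safety summary. Report tutor-recorded events separately, as class-phase surveillance in the programme arms.
- Align the Outcomes sentence with the reporting system in the Study overview: state who supplies reports from the control hubs, after the classes end, and from the testing sessions and device wear.

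The cost is a few items at sessions already planned, with no extra visits and no change to the sample size. Self-reported events depend on recall. Anyone who misses a session is not asked, and for those who drop out the reasons already collected remain the fallback.

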**Methods:**

The trial is set in eight Local Sports Partnership (LSP) hubs that have structured physical activity programmes. The hubs are the units of randomisation (clusters), and individuals are the units of analysis (participants). Eligible participants will contact one of the hubs, with each hub running four physical activity programmes. Each programme requires between 12–15 inactive adults, resulting in 48–60 participants per hub. Allowing for 20% dropout rate, an additional 96 people will be recruited giving a maximum sample of 576. The hub will be randomised: true control, usual programme or MFL intervention. The true control group will be given information about physical activity but will not be included in a programme for the duration of the trial; the intervention will involve the instructor training one (or more) of the participants to be a peer mentor using an educational toolkit; and usual care groups will have physical activity classes delivered as normal. Baseline data will collect physical activity measures and follow-up measurements will be obtained at 3 and 6 months. All participants will be asked to wear a device for measuring activity on the thigh (activPAL) for 7 days before commencing the programme and at 3 and 6 months. The primary objective of the study is to investigate if it is feasible to deliver the intervention and collect data on moderate to vigorous physical activity (MVPA) on all participants, thereby providing valuable information to guide sample size calculation for a future, more definitive trial.

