### Description of comparator intervention

The physical activity programmes in the comparator intervention will be run by the LSPs at existing exercise hubs in community settings. The programmes were developed as part of Ireland’s national physical activity plan, ‘Get Ireland Active’ [28]. These programmes run nationally and their purpose is to encourage and support physical activity by facilitating access to a wide range of physical activity opportunities in local communities. For Move for Life, four existing LSP programmes were identified as suitable for inactive adults aged 45 + years. Two programmes are gender segregated: ‘Men on the Move’ and ‘Women on Wheels’, both are 12-week structured exercise classes involving general sport, physical activities and cycling. ‘Get Ireland Walking’ is an 8-week walking initiative for inactive men and women; ‘Go for Life’ is an 8-week structured exercise class that typically recruits older adults aged 65 years plus. For the purposes of the comparator intervention in this trial, these programmes will run in the usual way so that participants are exposed to a community-based structured physical activity programme. Participants in the intervention arm of the trial will have these programmes augmented by the Move for Life intervention.

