### Data collection

The data collection team will conduct the physical tests, apply the activPAL device and facilitate completion of a questionnaire by all participants. After eligibility has been confirmed and informed consent has been obtained, MFL participants will complete a questionnaire comprising of four modules: behavioural change techniques, well-being; healthcare resource use and out-of-pocket expense and demographics (Additional file 3). They will then undergo a set of physical health assessments, including body mass index (BMI) and waist circumference. Validated tests of functional ability including balance and strength testing will be carried out including grip strength and the TUG test. Other parameters for testing include physical function (6-min walk test), falls risk and dual-task ability (dual-task timed up and go test), stand balance (single leg stand) and lower body strength (single and repeated chair to standing).

Physical activity outcomes (MVPA and daily sedentary time) will be measured using the activPAL, a small (9 g) device worn on the thigh. This device adheres to the right thigh, protected by a waterproof dressing. Participants will be asked to wear it continuously for seven days, and it will record physical activity and body posture (sitting, lying, standing or walking) via tri-axial accelerometer technology. The device has been selected because it records both activity and sedentary time with a high degree of accuracy, and it is well tolerated, producing long continuous wear periods [37, 38]. Data will be processed to identify daily time in bed (detected by a proprietary algorithm), daily standing time, daily time spent sedentary, daily time spent in light physical activity and in moderate to vigorous physical activity. Time spent in light and moderate to vigorous activity will be derived from the triaxial accelerometer data using the cut points validated by Powell et al. [39]. These additional behaviours may impact health in an older population. The testing team who take measurements and process accelerometer data will be blinded as to the trial status of each cluster.

Additional file 2 contains the entire testing protocol that will be carried out at baseline, immediately after testing and 3 months post intervention. Information for the process evaluation will be collected on an ongoing basis during the study (Fig. 3).

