**Fig. 3 Fig3:**
[figure not shown]
Timeline for the Limerick hubs

Interviews of stakeholders involved in previous physical activity programmes were conducted between January and March in order to inform the intervention development. From January to April, the team has developed the intervention. The trial commences in May and 8 weeks before commencing, and recruitment strategies have been developed. Four weeks beforehand, information sessions will take place. The trial will commence with recruitment, enrolment and baseline testing in Limerick hubs in May until July and in Clare from August until October. Follow-up testing at 3 and 6 months will follow for the hubs in Limerick and Clare.

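### Two follow-up schedules that cannot both hold: 3 and 6 months, or the end of the intervention and three months later, about five weeks apart for the 8-week programmes

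*Protocol article*

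**What the plan says.** All of the following is current text in the protocol article.

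**Calendar schedule.** The abstract and the Study overview state that "follow-up measurements will be obtained at 3 and 6 months". For the activity device, the Study overview covers every group: wear is "for 1 week before commencing the programme and again at 3 and 6 months". The timeline paragraph after Fig. 3 repeats it: "Follow-up testing at 3 and 6 months will follow for the hubs in Limerick and Clare".

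**Programme-anchored schedule.** Outcomes says: "At specific time-points, immediately post intervention and 3 months post intervention, follow-up testing sessions will take place". Data collection describes the testing protocol as "carried out at baseline, immediately after testing and 3 months post intervention".

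**Programme lengths.** Description of comparator intervention gives 12 weeks for Men on the Move and Women on Wheels, and 8 weeks for Go for Life. Get Ireland Walking "is an 8-week walking initiative for inactive men and women". Of the augmented programme, Development of the intervention says: "It can be adapted for 8, 10 or 12 weeks depending on the duration of the particular MFL programme strand".

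**True control.** Two of the eight hubs (Study design) run no programme while the trial lasts (Study overview, Randomisation process).

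**Where the visits are used.** Outcomes defines minimum thresholds as the least share of participants who attend the post-intervention and 3-month testing and give reliable data. Progression criteria stops progression if more than 40% fail to give reliable activity data, and names no visit.

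**The concern.** The two schedules coincide only if a programme lasts three months, and half of the listed programmes last 8 weeks. For an 8-week class, a week-8 reading describes activity while instructor-led classes are just ending. A week-13 reading describes activity about five weeks later, when the group is meant to be continuing on its own. Since the intervention aims at continued activity after the programme, these are different quantities.

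The trial is meant to show that moderate to vigorous activity can be measured, and to supply estimates for sizing a definitive trial. Completion rates and activity estimates by visit are hard to interpret if a visit means different elapsed times in different classes. The same ambiguity reaches the decision to progress, because the visit at which the 40% is to be counted is not identified.

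**Working it through.** **Inputs.** Programme lengths L = 8 and 12 weeks (Description of comparator intervention), and 10 weeks as a possible strand (Development of the intervention). One month = 365.25 / 12 / 7 = 4.348 weeks, so 3 months = 13.04 weeks and 6 months = 26.09 weeks.

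**Formulae.** Under the programme anchor, the first visit is at L and the second at L + 13.04 weeks from programme start. Under the calendar schedule the visits are at 13.04 and 26.09 weeks, counted here from programme start. That origin is an assumption, since the article states none.

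| Programme length | Programme anchor, visits 1 and 2 (weeks) | Calendar, visits 1 and 2 (weeks) | Gap at each visit (weeks) |
|---|---|---|---|
| 12 weeks | 12.0 and 25.0 | 13.0 and 26.1 | 13.04 − 12 = 1.0 |
| 10 weeks | 10.0 and 23.0 | 13.0 and 26.1 | 13.04 − 10 = 3.0 |
| 8 weeks | 8.0 and 21.0 | 13.0 and 26.1 | 13.04 − 8 = 5.0 |
| True control (no programme) | cannot be dated | 3 and 6 months, origin not stated | – |

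The stated 3 and 6 months is therefore reproduced to within about a week for the 12-week programmes, but not for the 8-week ones. Within the programme anchor, 8-week and 12-week classes are 12 − 8 = 4 weeks apart at both visits.

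**How many are affected.** The article does not give numbers by programme. With equal group sizes (assumption), a hub running all four programmes has 2/4 = one half of its participants in 8-week classes. The Discussion allows some hubs to run three programmes, which gives 1/3 to 2/3.

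**Intervention against usual programme, programme anchor, equal group sizes.** Mean first-visit time is (8 + 8 + 12 + 12)/4 = 10.0 weeks for a four-programme hub. It is (8 + 8 + 12)/3 = 9.3 weeks if a 12-week programme is dropped, and (8 + 12 + 12)/3 = 10.7 weeks if an 8-week one is dropped. With the same mix the difference is zero. With opposite omissions it is 10.67 − 9.33 = 1.3 weeks.

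**The 3-month label.** In the Study overview the 3-month visit is the first follow-up. In the Outcomes definition of minimum thresholds it is listed after the post-intervention visit, so it is the second. For an 8-week class, that makes the same label week 13 in one place and week 21 in the other.

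**The case against.** The fair case against is that one wording is loose shorthand for the other. For 12-week programmes the gap is about a week, and the calendar schedule appears in three places, once for all groups. Fig. 3 and the additional file with the full testing protocol are not shown here and may give dates. The trial is a feasibility study in which any modelling is exploratory, and nothing shows that a shift of a few weeks would move the share giving reliable data. Anchoring on programme end is also a defensible choice where the aim is to keep people active once classes finish.

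Much of this stands, and it rules out several stronger readings that a reader might infer:

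- *True controls have no visit dates at all.* Not supported. The Study overview gives all groups 3 and 6 months. Controls lack a date only under the programme-anchored wording. Under the calendar wording, what is loose is the origin.
- *The arms will be measured at different times.* Not supported as a general statement. Unequal timing arises only under the wording in Outcomes and Data collection. Intervention and usual-programme hubs draw on the same four programmes, so their timing differs only if their mixes differ. Setting classes tested at programme end against controls tested at 3 months describes a hybrid schedule that the article does not state.
- *There is a third schedule in Data collection.* Its first follow-up, placed after testing, is evidently a slip for after the intervention.
- *Season is overlooked.* The Discussion already raises daylight and staggered starts, and plans to relate results to daylight hours.

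What does not stand is the shorthand defence for the 8-week programmes, where the gap is five weeks. Nor can it be assumed that the unseen material settles the matter: the article describes the testing protocol in programme-anchored terms and the timeline in calendar terms.

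**Conclusion.** The article contradicts itself on when follow-up takes place. The gap is about 1 week per visit for the two 12-week programmes and about 5 weeks per visit for the two 8-week programmes. Under the programme-anchored wording, 8-week classes are tested 4 weeks before 12-week classes, and two of the eight hubs have no datable visit. Separately, the visit to which the minimum threshold, and hence the 40% reliable-data criterion, refers is unclear.

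The week counts rest on the stated programme lengths, on average calendar months and on counting from programme start. Any share of participants affected also rests on equal group sizes. No bias between arms, and no effect on the 40% figure, has been shown. This should be corrected before follow-up testing, because visits held at inconsistent times cannot be realigned afterwards.

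**What to change.** - Reconcile the article to one measurement schedule for all three arms. The simplest choice is the 3 and 6 months already stated for all groups.
- State one origin: the hub's start date and, for control hubs, the date on which allocation takes effect. Apply one common visit window.
- Amend Outcomes and Data collection to match, including the slip in the latter, and use the 3-month label for one visit only.
- Name in Progression criteria the visit, or visits, at which the 40% reliable-data criterion is assessed.
- In the programme arms, record weeks since the last class as a descriptor, so that end-of-programme and maintenance readings can be told apart.

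The cost is wording and scheduling. The downside is that the first visit for 8-week classes falls 13 − 8 = about 5 weeks after the last class, so it is no longer an end-of-programme reading. The descriptor makes this visible but does not replace that reading.
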